**Methods:**

A single-center, randomized controlled trial of pediatric patients with acute lung injury after surgery for congenital heart disease who will receive prone position ventilation or usual care (control group). A total of 68 children will be enrolled according to the inclusion criteria. The main outcome measures will be lung compliance and oxygenation index. The secondary outcomes will be duration of mechanical ventilation, length of stay in cardiac intensive care unit, reintubation rate, and complication rate.

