### Intervention strategies

The family members of the subjects will be informed about the purpose and methods of prone position ventilation, and their consent will be obtained for participation in the study.Careful assessment of the disease status will be performed and adequate fixation of the various cannulas and vascular catheters will be ensured.Enteral nutrition will be suspended 30 min before and the gastrointestinal nutrition tube will be closed before preparing for prone positioning.The timing of start of prone position ventilation will be determined by a team of medical personnel after determining the following: (1) the child has a stable circulation and shows no restlessness, and (2) the routine medical care has been provided.The child will be placed in the prone position with the participation of researchers, doctors, and the nursing staff. The child’s head will be tilted to one side to avoid damage to the eyes and nose due to compression; the arms will be bent upwards and placed on both sides of the head in a W-shaped configuration. The arms can also be placed in another position depending on the specific situation. Both lower limbs will be bent downwards to form an “M” shape; soft pillows will be used below both knee joints to avoid compression.Meticulous care will be exercised to ensure smooth fixation of mechanical ventilation, endotracheal tube, and various catheters.The depth of sedation will be calibrated during the entire prone position ventilation period to achieve good man-machine synchronization.Requirements during prone position ventilation: (1) adequate suction of the sputum and (2) the mechanical ventilation tube is suspended in the air, and the head is in left or right side position for 1–2 h.In a crossover design, the prone position will be maintained for 6–8 h per day until the improvement in oxygenation index (mean airway pressure × FIO_2_ × 100)/PaO_2_). Oxygenation index exceeding the baseline value or chest X-ray or CT findings suggest lung tissue recruitment. Prone position will be discontinued in case of deterioration of the condition (such as development of hemodynamic instability, pneumothorax, mediastinal emphysema, catheter loss, facial trauma, or formation of pressure ulcer).

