## Outcomes

### Outcomes (effectiveness)

Main outcome indicators: lung compliance, SPO_2_, respiratory rate, peak, positive end-expiratory pressure (PEEP); laboratory indices: oxygenation index (mean airway pressure × FIO_2_ × 100)/PaO_2_), oxygen partial pressure (PaO_2_), carbon dioxide partial pressure (PaCO_2_), pH; chest radiograph.Secondary outcome indicators: (1) duration of mechanical ventilation; (2) length of stay in cardiac intensive care unit (CICU); (3) incidence of reintubation; (4) incidence of complications: pressure skin injury, slippage of the intubation, compression, and displacement of the pipeline; (5) hemodynamic stability: heart rate (HR), invasive arterial blood pressure (ABP), central venous pressure (CVP).

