### Assessment of risks and benefits

All subjects will be closely monitored for adverse events. The incidence of pressure ulcers, wound infection, unplanned rechecks, and catheter slippage will be recorded. These data will be published along with the main results of the study. Personal and telephonic meetings will be regularly conducted to ensure close coordination between the research teams.

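### The complication outcome and the list of recorded adverse events do not match, and neither names the air-leak events that the protocol itself treats as deterioration

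*Protocol article*

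**What the plan says.** The Methods part of the Abstract names complication rate as a secondary outcome: "duration of mechanical ventilation, length of stay in cardiac intensive care unit, reintubation rate, and complication rate". Outcomes (effectiveness) gives it content as the fourth secondary indicator: "incidence of complications: pressure skin injury, slippage of the intubation, compression, and displacement of the pipeline". The items follow a colon, and nothing marks them as examples.

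Two other places in the protocol article list harms:

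- Intervention strategies discontinues prone positioning on deterioration and gives as examples "development of hemodynamic instability, pneumothorax, mediastinal emphysema, catheter loss, facial trauma, or formation of pressure ulcer".
- Assessment of risks and benefits opens with "All subjects will be closely monitored for adverse events". It then states: "The incidence of pressure ulcers, wound infection, unplanned rechecks, and catheter slippage will be recorded". Those data are to be published with the main results.

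Two further indicators in Outcomes (effectiveness) bear on the point. Circulation is a separate secondary outcome, "hemodynamic stability: heart rate (HR), invasive arterial blood pressure (ABP), central venous pressure (CVP"). The chest film is listed among the main indicators: "carbon dioxide partial pressure (PaCO_2_), pH; chest radiograph".

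**The concern.** Complication rate is a named outcome in a small trial of turning infants prone after cardiac surgery, so readers will look to it for the harm comparison. Its content covers skin, tube and line events only. The air-leak events that the protocol considers serious enough to end the intervention are outside it, and they are also outside the list of incidences to be recorded and published.

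Other parts of the article show that these events matter to its authors. The exclusion criteria keep out infants with severe pneumothorax or facial trauma, so either one seen later would be new. The Background supports the safety of prone positioning partly with a cited study that found no difference in air leakage between positions. Quality control keeps infants who deteriorate rapidly in the intention-to-treat analysis. If the cause was an air leak, though, the complication rate would not show it.

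The two reporting lists also disagree with each other. A team choosing between them would obtain different complication rates from the same infants.

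**Working it through.** The plan states no figure on this point, so there is none to reproduce. The check sets the three lists side by side.

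| Event | Ends prone positioning (Intervention strategies) | Complication outcome (Outcomes) | Incidence recorded and published (Assessment of risks and benefits) |
|---|---|---|---|
| Pressure ulcer or pressure skin injury | yes | yes | yes |
| Loss or slippage of tube or catheter | yes | yes, broadly | yes |
| Haemodynamic instability | yes | not as an event; HR, ABP and CVP are a separate outcome | no |
| Facial trauma | yes | not named; a pressure-type injury might count | not named; a facial pressure ulcer might count |
| Pneumothorax | yes | no | no |
| Mediastinal emphysema | yes | no | no |
| Compression | no | yes | no |
| Wound infection | no | no | yes |
| Unplanned rechecks | no | no | yes |

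Of the six stopping events:

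- two have a counterpart in the reporting lists (pressure injury, catheter loss);
- one is followed only through measured values (haemodynamic instability);
- one is covered at most in part (facial trauma);
- two have no counterpart at all (pneumothorax, mediastinal emphysema).

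Between the two reporting lists, compression appears only in the outcome, and wound infection and unplanned rechecks appear only in the risk section.

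**Illustration of scale.** The group size, 34, comes from Sample size/power calculation. The per-infant risk p of an uncounted event is not in the document. The values below are assumptions, and infants are taken as independent. The expected number uncounted is 34 × p, and the chance of at least one is 1 − (1 − p)^34.

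| Assumed p | Expected uncounted in 34 | Chance of at least one |
|---|---|---|
| 1% | 0.34 | 29% |
| 3% | 1.02 | 64% |
| 5% | 1.70 | 83% |
| 10% | 3.40 | 97% |

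The effect on a rate, again with assumed inputs and with listed and unlisted events independent, is 1 − (1 − listed) × (1 − p):

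- With a listed rate of 5% and p from 1% to 5%, the rate with the extra events is 1 − 0.95 × 0.99 = 5.95% up to 1 − 0.95 × 0.95 = 9.75%.
- With a listed rate of 10%, it is 1 − 0.90 × 0.99 = 10.9% up to 1 − 0.90 × 0.95 = 14.5%.

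These figures show only that the omission could be small or could nearly double the rate. They do not estimate it.

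**The case against.** The strongest reply is that the lists serve different purposes. Reasons to stop an intervention, an outcome item on skin and tube problems, and an adverse-event section need not be identical. The risk section promises monitoring of all subjects, which covers both arms and is not restricted by type of event. Chest radiographs are a main indicator and are the kind of image on which an air leak would be seen. Haemodynamics and reintubation are outcomes in their own right, so the complication item is not the only harm evidence. This is also a condensed article, and adverse-event definitions and form fields commonly sit in the full protocol or analysis plan.

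Much of this stands, and it rules out several stronger readings that a reader might infer:

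- *The rate will understate harm.* It does so only if such events occur and do not also count under a listed item. No rates are given, so only *can* is supported.
- *Nothing would prompt recording in control infants.* The monitoring sentence covers them. The narrower fact is that, as events during the trial, air leak and facial trauma are named only as reasons to stop prone positioning.
- *Three of the six stopping events are wholly absent.* The firm count is two. Intervention strategies describes facial harm partly as a compression injury, which could fall within the outcome's wording.
- *Wound infection goes unreported.* It lies outside the complication outcome, but it is recorded and published.
- *The comparison is biased towards prone positioning.* The direction cannot be derived, since air leaks could occur in either arm.

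What the reply does not remove is the mismatch. Monitoring and imaging may find an air leak, but no sentence carries it into the complication rate or the named incidences, and the radiograph has no stated link to these events. The allowance for a condensed article does not help here, because the article itself fixes the content of the outcome.

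**Conclusion.** The point holds as an inconsistency in how harm is defined. The complication outcome and the recorded incidences differ from each other. Both leave out pneumothorax and mediastinal emphysema, and facial trauma is covered at most in part, although the protocol treats all three as deterioration. A team following the text would report a complication rate without air-leak events, and that rate can understate harm.

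The size is unknown because the document gives no event rates, and the effect on the comparison between arms has no derivable size or direction. The illustrative chance of 29% to 97% of at least one uncounted event in 34 prone infants rests wholly on assumed risks of 1% to 10%. The main outcomes and the sample size are not affected.

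**What to change.** Reconcile the outcome item in Outcomes (effectiveness) and the list in Assessment of risks and benefits into one harm list. Add pneumothorax, mediastinal emphysema, facial trauma and haemodynamic instability as events, and keep wound infection. If unplanned rechecks and compression stay, say what each means, since neither is defined.

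Record the list in the same way and over the same period in both arms, and report each event by arm. A single pooled rate should not carry the comparison, because it would weigh a displaced line the same as a pneumothorax.

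The stopping reasons in Intervention strategies stay as they are, since this point concerns only what is counted and reported. The cost is a wording change and a few more case report form items, drawing on films and monitoring already in the trial. The downside is a possibly higher reported complication rate.

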### Sample size/power calculation

According to pre-experimental investigations, the average oxygenation index required by the experimental group of children is 276, with a standard deviation of 68, and the control group has an average oxygenation index of 228, with a standard deviation of 67. Comparing the two independent sample means, *α* = 0.05, *β* = 0.2, the Gpower sample calculation software showed an effect size of 0.71. The ratio of the test group and the control group is 1:1. An attrition rate of 10% has been factored in the sample size calculation. The calculated sample size is 34 patients per group and total sample size is 68 patients.

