## Participants and recruitment

### Inclusion and exclusion criteria

A total of 68 infants who qualify the following criteria will be included in the study:
PALI after surgery for congenital heart disease or patients in whom chest X-ray and CT findings indicate PALI. The diagnostic criteria for PALI: (1) acute onset; (2) hypoxemia, oxygenation index ≥ 4; and (3) chest radiograph showing bilateral lung infiltratesInvasive mechanical ventilationAge range: 0–12 monthsPatients with stable hemodynamic status, more than 72 h after surgery. Hemodynamic stability defined as Inotropes stable (IS < 10) or based on ECHO (ejection fraction > 50%)Informed consent of family membersThis study has been approved by the Ethics Committee of the Children’s Hospital of Fudan University, No. (2020) 130

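### The sample size is built on oxygenation index values (276 vs 228) that do not fit the index as the protocol defines it, in scale or in direction, so power for the defined endpoint is unknown

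*Protocol article*

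**What the plan says.** All references are to the protocol article.

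- **Abstract, Methods:** lung compliance and oxygenation index are the main outcome measures.
- **Outcomes (effectiveness):** the index is listed among the main outcomes with its formula, "oxygenation index (mean airway pressure × FIO_2_ × 100)/PaO_2". The Intervention strategies section prints the same formula.
- **Inclusion and exclusion criteria:** the second diagnostic criterion is "hypoxemia, oxygenation index" of at least 4.
- **Intervention strategies:** immediately after the formula, an index above the baseline value is given as one of the signs that lung tissue has been recruited.
- **Sample size/power calculation:** "the average oxygenation index required by the experimental group of children is 276, with a standard deviation of 68". For controls the figures are a mean of 228 and an SD of 67. The section adds that "the Gpower sample calculation software showed an effect size of 0.71", with α = 0.05, β = 0.2, 1:1 allocation and 10% attrition, giving 34 per group and 68 in total.
- **Statistical analyses:** oxygenation indices are to be compared between groups by a t test.

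No section defines a second index or says that the sample size uses a different measure from the outcome.

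**The concern.** PaO2 is in the denominator of the printed formula, so the index rises as oxygenation worsens. The eligibility criterion agrees, since hypoxemia is a value at or above a single-digit cut-off. The sample size section uses the same name for values in the hundreds and gives the higher mean to the arm that is expected to benefit. The recruitment sentence under Intervention strategies also treats a rise as good.

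Two things are at stake. First, a standardised difference of 0.71 on one quantity does not carry over to another that is a reciprocal multiplied by a further variable, so the 80% power may not belong to the endpoint that will be analysed. Second, when one name covers quantities with opposite signs, a between-group difference can be reported as benefit when the printed formula says harm.

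**Working it through.** **1. Reproduce the stated sample size.** Inputs are from the Sample size/power calculation section; a two-sided test is assumed, because sidedness is not stated.

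- Pooled SD = √((68² + 67²)/2) = 67.5; d = (276 − 228)/67.5 = 0.711. This matches the stated 0.71.
- Normal approximation: n = 2 × (1.960 + 0.842)² / 0.711² = 31.04 per arm. With 10% attrition, 31.04 × 1.1 = 34.1 or 31.04/0.9 = 34.5. The stated 34 is reproduced.
- With 34 × 0.9 ≈ 31 evaluable per arm, power is 79.9% by the normal approximation and 78.7% by the t test.

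The calculation is sound for its inputs. The question is what the inputs measure.

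**2. Scale.** 276/4 = 69 and 228/4 = 57, so the means are 57 to 69 times the entry threshold. Solving the printed formula for PaO2 (FiO2 as a fraction, PaO2 in mmHg) gives PaO2 = pressure × FiO2 × 100 / index. The pressure and FiO2 values below are assumptions.

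| Mean airway pressure | FiO2 | PaO2 if index = 276 | PaO2 if index = 228 |
|---|---|---|---|
| 10 | 0.4 | 1.4 | 1.8 |
| 20 | 1.0 | 7.2 | 8.8 |
| 30 | 1.0 | 10.9 | 13.2 |

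None of these is credible as a group mean in hemodynamically stable infants.

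**3. Direction.** On the printed formula, 276 (prone) against 228 (control) says that prone infants are worse oxygenated.

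**4. Could units explain it?** If FiO2 was entered as a percentage and the factor of 100 kept, the figures would be 2.76 and 2.28 on the usual scale. Both are below the entry threshold of 4, and prone is still the worse arm. With PaO2 in kPa, an index of 276 at pressure 15 and FiO2 1.0 needs 15 × 100/276 = 5.4 kPa (about 41 mmHg), and that scale does not fit a threshold of 4. Neither reading repairs the direction.

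**5. What if the figures are PaO2/FiO2?** This is an inference; the document does not say so. The formula index equals 100 × pressure / (PaO2/FiO2). At an assumed pressure of 10 to 15, 276 becomes 3.6 to 5.4 and 228 becomes 4.4 to 6.6, which is near the threshold and in the order that favours prone.

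**6. Illustration of power on the formula index.** Assumptions: PaO2/FiO2 normal in each arm with the stated means and SDs, with values below a cut-off of 50 to 100 removed because the reciprocal is unstable near zero; pressure lognormal, independent of PaO2/FiO2, with the same distribution in both arms. The mean pressure does not affect d. Power is for a two-sided t test with 31 per arm; ranges are over the cut-off.

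| CV of pressure | d, raw scale | Power | d, log scale | Power |
|---|---|---|---|---|
| 0 | 0.60–0.63 | 64–69% | 0.68 | 74–75% |
| 35% | 0.40–0.42 | 34–36% | 0.42–0.45 | 37–41% |

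The comparison figure is about 79% at d = 0.71.

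**The case against.** The best reply is that this is a slip in a name. If the investigators meant PaO2/FiO2 all along, the figures are plausible, the direction is right, the arithmetic reproduces and the power statement stands; only wording needs repair. That has force. A reader might infer from the mismatch that the trial has no valid power statement at all. The document does not support that, because it does not show whether the formula or the figures are wrong.

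A reader might also take the lower powers above as the trial's true power. They are not. The document gives no airway pressure, no spread for it, no correlation with PaO2/FiO2 and no statement that the figures are PaO2/FiO2. The result also moves with the truncation cut-off and the analysis scale.

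It is also fair to say that a two-sided test has the same power in either direction. The reversal therefore changes how a result is read, not the number of infants.

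What the reply does not remove is the contradiction. The formula is printed twice, so anyone who computes the outcome as written will analyse an endpoint that the trial was not sized for. This is conflicting text in the protocol, not detail left to an analysis plan.

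**Conclusion.** The protocol is wrong as written: the endpoint definition and the sample size do not describe the same quantity. The scale mismatch (57 to 69 times the entry threshold) and the reversed direction follow from the document's own formula, threshold and figures. The only added premises are ordinary ranges for airway pressure and FiO2.

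The stated 80% power belongs to whatever quantity has means 276 and 228. For the index as defined, power cannot be determined from the document. If the figures are PaO2/FiO2 and the assumptions above hold, power would be below the stated level: about 69% to 34% on the raw scale and 75% to 37% on the log scale, for a CV of 0 to 35%. This is an illustration of sensitivity, not an estimate. If PaO2/FiO2 is the intended endpoint, the stated power applies to it.

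**What to change.** Name one quantity, with one formula and one direction of benefit, as the endpoint in the Abstract, Outcomes, Sample size/power calculation and Statistical analyses sections. The eligibility criterion and the Intervention strategies text (its formula and its reading of a rise above baseline) must be reconciled with that choice. Which clinical rule is right there is for the investigators to decide.

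- **If the formula index is the endpoint:** re-derive means and SDs from the pilot data, provided that airway pressure, FiO2 and PaO2 were recorded, which the article does not say. The log scale is preferable because the index is a skewed ratio. Then restate effect size and power for 68 infants.
- **If PaO2/FiO2 was intended:** correct the name and formula of the outcome wherever they appear. The existing calculation then stands for that endpoint.

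The cost is protocol wording and, in the first case, a recalculation. The restated power may be less favourable. No extra patients are needed to restate it, though holding 80% power on the formula index could require more.

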### Block randomization

The block length will be determined along with all possible permutations of the two groups. Setting a block length of 4, all possible arrangements of the intervention group (A) and the control group (B) are AABB, BBAA, ABAB, BABA, BAAB, and ABBA.The sampling numbers will be assigned to each possible permutation block.According to the sample size, the number of blocks will be determined. The sample size of this study is 68, and the number of blocks is 68/4 = 17.The random number function in the computer Excel program will be used to generate 5 integer sequences between 1 and 6, corresponding to the above-mentioned block assignment number; the generated sequence will be numbered and placed in the corresponding numbered sealed opaque envelope.Another researcher (not involved in the implementation of intervention measures) will select the research subjects who qualify the exclusion and inclusion criteria and will open the envelope in the order of the numbers on the envelope.

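### The randomisation text needs 17 blocks of four but generates 5 numbers to choose them; separately, one researcher both selects infants and opens envelopes from fixed blocks of four

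*Protocol article*

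**What the plan says.** All of this is in the protocol article.

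- **Block length** (Block randomization): "Setting a block length of 4, all possible arrangements of the intervention group (A) and the control group (B) are AABB, BBAA, ABAB, BABA, BAAB," with ABBA as the sixth.
- **Number of blocks** (same section): "The sample size of this study is 68, and the number of blocks is 68/4 = 17".
- **Numbers generated** (same section, next sentence): "The random number function in the computer Excel program will be used to generate 5 integer sequences between 1 and 6", each integer standing for one of the six arrangements.
- **Envelopes** (same section): "the generated sequence will be numbered and placed in the corresponding numbered sealed opaque envelope". The text does not make clear whether one envelope serves one infant or one block.
- **Who enrols and who opens** (same section): a researcher outside the delivery of the intervention "will select the research subjects who qualify the exclusion and inclusion criteria and will open the envelope in the order of the numbers".
- **Ratio** (Sample size/power calculation): "The ratio of the test group and the control group is 1:1", with 34 infants per group.

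Trial design makes this a single-centre study. Blinding says that families cannot be blinded, that the order system is open only to the responsible nurses, and that the nurses handling data entry and statistics are blinded. It does not mention the researcher who opens the envelopes. Trial status reports the preliminary experiment as finished and follow-up as ongoing.

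**The concern.** There are two separate issues.

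The first is a plain inconsistency. An integer from 1 to 6 identifies one of the six permutations, so one integer is needed per block. The section calculates that 17 blocks are needed and then describes generating 5 numbers. Someone following the text literally would not have a list for the whole trial, and nothing says how later infants would be allocated. Every between-group comparison rests on that list.

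The second is concealment. Sealed opaque envelopes hide the next allocation physically, but they do not prevent deduction. A person who knows the block length and has seen the earlier allocations can sometimes work out the next one. Here the person who opens each envelope, and so sees every allocation, also decides which infants enter. Some entry criteria leave room for judgement, notably the radiological findings, and family consent is needed as well. Foreknowledge could therefore affect who is approached and when. With 34 infants per arm and unadjusted tests under Statistical analyses, a few steered enrolments could shift baseline oxygenation between the arms.

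**Working it through.** **1. The stated number of blocks.** Inputs: N = 68 and block length 4 (Block randomization). 68 / 4 = 17, which reproduces the article's figure. 17 × 4 = 68 allocations, 34 per arm, in line with the 1:1 ratio.

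**2. What five integers would cover.** 5 × 4 = 20 allocations, and 20/68 = 29%. The shortfall is 17 − 5 = 12 blocks, or 12 × 4 = 48 infants, and 48/68 = 71%. If the phrase means five sequences, each of several integers, their length is not given. The list is then undefined, and the figure 17 is still not carried through.

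**3. Allocations certain in advance.** Assumptions: one envelope per infant, and a recruiter who knows the block length and all past allocations. In AABB and BBAA the last two positions are determined. In each of the other four permutations only the last is. The expected number per block is (2 × 2 + 4 × 1)/6 = 1.33. That is 1.33/4 = 33%, and 68 × 0.333 = 22.7, or about 23 infants.

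**4. Correct guesses.** Under the same assumptions the recruiter always guesses the arm with more places left in the block.

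| Position in block | Probability correct |
|---|---|
| 1 | 1/2 |
| 2 | 2/3 |
| 3 | 1/3 × 1 + 2/3 × 1/2 = 2/3 |
| 4 | 1 |

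The sum is 2.83, and 2.83/4 = 70.8%, about 48 of 68, against 50% under simple randomisation.

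**5. If one envelope held a whole block.** Opening it for the first infant would show the next three allocations: 3 × 17 = 51 of 68. The wording allows this reading but does not state it.

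**6. Effect of varying the block size.** Lists of 68 were simulated with each size equally likely.

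| Block sizes | Correct guesses | Certain from running imbalance alone |
|---|---|---|
| Fixed 4 | 70.8% | about 8% |
| 4 and 6 | about 69% | about 1% |
| 4, 6 and 8 | about 68% | about 0.1% |

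The last column understates what a better-informed recruiter could deduce. A further simulation (4,000 lists) assumed a recruiter who knows which sizes are in use, but not their order, and updates on every past allocation. With sizes 4 and 6, about 5.5% of allocations are then certain, against 33% for fixed blocks of four. Correct guesses stay at about 69%. A 2/4/6 mix leaves correct guesses at about 70%, because a block of 2 is guessed correctly (1/2 + 1)/2 = 75% of the time.

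**The case against.** The strongest reply on the first issue is that 5 is a slip or a loose translation. The preceding sentence gives 17, so the intended length is on the page. A reader might infer that the list ran out during the trial or that most infants were never properly randomised. The article does not support that: it speaks of integer sequences rather than five integers, and it does not report what was generated. The shortfall of 48 is therefore conditional. The contradiction is not, and because follow-up is under way, correcting the text alone would not show what was done.

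On the second issue, the article states real safeguards: sealed, opaque, numbered envelopes opened in order by someone outside the intervention, a restricted order system, and blinded data staff. A reader might infer that allocation is simply predictable. It is not: on average two thirds of allocations are not determined, and the 33% requires that the researcher knows the block length and tracks the sequence. The article does not say the researcher is told it. A reader might also stress that bedside staff see the position, but the argument needs only the envelope-opener's own knowledge. Discretion over eligibility is limited too. Haemodynamic stability has numerical criteria (IS below 10 or ejection fraction above 50%), and the oxygenation index, age and time since surgery are also numerical. Radiology and some exclusions still leave room for judgement.

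Fixed blocks of four are a legitimate choice in themselves, and detailed enrolment logging may be in the full protocol. What survives is the combination the article does state: fixed blocks of four, one centre, and one person who both selects infants and opens the envelopes.

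**Conclusion.** The contradiction between 17 blocks and 5 generated numbers holds without any outside figure and must be corrected. On the reading that five integers are meant, the list covers 20 of 68 infants and leaves 48 (71%) without an allocation. Whether that happened in practice cannot be told from the article.

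The concealment point holds as a secondary one. Partial predictability, with 33% of allocations certain and 70.8% guessed correctly, depends on the researcher knowing the block length, tracking past allocations and having one envelope per infant. These figures measure opportunity. They are not evidence that any enrolment was steered.

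**What to change.** - **Correct the number.** State that 17 integers between 1 and 6 are generated, or that a complete list for all 68 infants is produced before recruitment. If the sample size is revised, the number of blocks must follow.
- **Report what was done.** State how many block numbers were generated, when, and how any infants beyond that list were allocated.
- **Reduce deduction for infants still to be allocated.** Use randomly varied block sizes without size 2, for example 4 and 6, and do not disclose them to the recruiting researcher. State that each envelope holds one infant's allocation. Record eligibility and consent before the envelope is opened.

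The main gain from varied blocks is the removal of most of the allocations that are certain in advance. Average guessability falls only from 70.8% to about 69%, so recording eligibility and consent first is needed as well.

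The cost is a revised paragraph, a new list and a possible slight imbalance. With blocks of 4 and 6 the running difference between arms never exceeds 3. It must be even at 68 infants, so the final difference is at most 2 (35 versus 33).
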